#### Statistical Analysis of Other Outcomes

Other study parameters and basic characteristics will only be explored to test for differences between the study groups. If there are found to be significant differences with clinical relevance for the primary outcome, this will be taken into account when analyzing the data by incorporating these differences in the linear mixed model.

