The optimal initial oxygen concentration for stabilizing infants after birth is still a subject of debate, as both hypoxia and hyperoxia can cause damage of multiple organ systems (16, 17). Hypoxia may lead to delayed cellular damage, (18) as during hypoxia the production of free radicals will be provoked, by an elevated level of hypoxanthine (19). On the other hand, high oxygen levels increase the biosynthesis of prostaglandins which are an additional mechanism inhibiting chemoreceptors in the respiratory center (20). In addition, free radical production (associated with both oxidative and nitrosative stress) increases during hyperoxia, which can overwhelm the relatively immature antioxidant capacity of the preterm infant. The resulting excess of free radicals cause wide-spread damage to cells, enzymes, lipids, DNA, and proteins (21–24).

The recent meta-analysis of Oei et al. showed a higher mortality rate in the group of preterm infants (< 32 weeks of gestation) resuscitated with an initial FiO_2_ of 0.21 compared to the group resuscitated with an initial FiO_2_ of 1.0 (18). Furthermore, when stabilization of preterm infants after birth was started with low oxygen concentrations (FiO_2_ 0.21–0.3), oxygen saturation (SpO_2_) and heart rates increased more slowly than the SpO_2_ references outlined in the international guidelines, despite the use of respiratory support. This indicates that when starting respiratory support with lower oxygen concentrations preterm infants are at a higher risk for hypoxia (25). Indeed, this was shown in the study of Goos et al. (12) and White et al. (13).

Regardless of the initial FiO_2_ level, in all studies most infants ended up with a FiO_2_ between 0.4 and 0.6 after 5 min to reach SpO_2_ target ranges. Currently, to prevent hyperoxia and achieve normoxia in newborns, international guidelines recommend to start stabilization after birth in preterm infants with low FiO_2_ (0.21–0.3) (26), after which FiO_2_ should be titrated based on SpO_2_ target ranges (16, 17, 27). In this recommendation, a period of low oxygen saturation is accepted and the effect of hypoxia on respiratory effort seems to be disregarded (28).

We hypothesize that with an initial FiO_2_ of 1.0, infants will reach SpO_2_ target ranges more rapidly, leading to less hypoxia and an increase in respiratory effort. With careful titration of FiO_2_ based on SpO_2_ target ranges, we hypothesize that the occurrence of hyperoxia will be minimized.

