### Other Outcomes

Other outcomes that will be collected include;

- Percentage of time of facemask ventilation applied during stabilization at birth- Average oxygen saturation and heart rate in the first 5 min after birth- Oxygen saturation and heart rate *per minute* in the first 5 min after birth- Percentage of spontaneous breaths with tidal volumes above 4 mL/kg- Percentage of time that oxygen saturation is within 90–95% range in the first 5 min after birth- Percentage of time that oxygen saturation is within 90–95% range between 5 and 10 min after birth- Percentage of time that oxygen saturation is within target ranges defined by Dawson et al. (27) in the first 10 min after birth.

In addition, we will collect basic characteristics such as gestational age, birth weight, mode of delivery, incidence of complications in pregnancy, use of antenatal corticosteroids, maternal medication use, and Apgar score 1 and 5 min after birth.

This study is not designed to demonstrate any differences in clinical short- and long-term outcomes. However, we will record study parameters focusing on short-term clinical outcomes, such as incidence of intubation in the delivery room and in the first 24 h after birth, pneumothorax, intraventricular hemorrhages (IVHs) grade 3 or more and neonatal death.

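### The covariate rule for the linear mixed model uses between-arm significance tests and admits variables measured after the allocated oxygen starts, so the model's group effect may no longer be the total effect of initial FiO2

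*Protocol article*

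**What the plan says.** Statistical Analysis of Other Outcomes gives the rule in two steps. First, "Other study parameters and basic characteristics will only be explored to test for differences between the study groups". Second, "If there are found to be significant differences with clinical relevance for the primary outcome, this will be taken into account", and the means of doing so is "by incorporating these differences in the linear mixed model". Selection therefore needs a significant difference between arms plus a judgement of clinical relevance. No variable is named, and nothing restricts the candidates to those fixed before randomisation.

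The candidates are listed under Other Outcomes. They include "Percentage of time of facemask ventilation applied during stabilization at birth", "Average oxygen saturation and heart rate in the first 5 min after birth", time within SpO2 ranges, and the share of spontaneous breaths above 4 mL/kg. The basic characteristics in the same section end with "maternal medication use, and Apgar score 1 and 5 min after birth".

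The Introduction states the expected mechanism: with an initial FiO2 of 1.0, "infants will reach SpO_2_ target ranges more rapidly, leading to less hypoxia and an increase in respiratory effort". The Discussion repeats it.

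The primary comparison of average minute volume is an unadjusted Student's t-test or Mann-Whitney test (Statistical Analysis of Primary Outcome). The linear mixed model appears under Statistical Analysis of Secondary Outcomes. It covers minute volume, tidal volumes, rate of rise and diaphragm activity over time, by study group, and also 8-iso-prostaglandin F2α.

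**The concern.** A covariate in a treatment-effect model should be something that treatment cannot have changed. Here the candidates include measurements that the allocated oxygen is meant to change, taken in the same five minutes as the outcome. A between-arm significance test is a poor filter for such variables, because it picks the ones that treatment has moved most. The clinical-relevance condition does not protect either, since SpO2 and heart rate are plainly relevant to breathing.

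For variables that really are baseline, randomisation means that a significant difference is a chance finding. The test then makes the covariate set depend on the data without identifying the variables worth adjusting for.

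At stake is the meaning of the mixed-model group effect on minute volume and the other respiratory measures. That effect is a secondary analysis, but it concerns the same variable as the primary outcome.

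**Working it through.** **1. The plan's own figure.** Inputs from Sample Size Calculation: difference 210 − 150 = 60 mL/kg/min, SD 70, two-sided α 5%, power 80%.

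n per arm = 2 × (1.960 + 0.842)² × 70² / 60² = 2 × 7.85 × 4900 / 3600 = 21.4, rounded up to 22. Allowing for 10% loss, 22 / 0.9 = 24.4, rounded up to 25 per arm and 50 in total. The stated figures reproduce, and the same inputs are used below.

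**2. Which candidates treatment can affect.**

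| Candidate (Other Outcomes) | When measured | Relation to minute volume |
|---|---|---|
| SpO2, time in SpO2 ranges | first 5 to 10 min | hypothesised pathway |
| Heart rate | first 5 min | response to oxygenation and breathing |
| Mask-ventilation time | during stabilisation | response to weak breathing |
| Share of breaths above 4 mL/kg | spontaneous breaths at birth | close to a component of the outcome |
| Apgar scores | 1 and 5 min | overlap with breathing |
| Gestational age, birth weight, mode of delivery, pregnancy complications, antenatal steroids, maternal medication | known before or fixed at birth | true baseline |

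The 1-minute Apgar score falls close to the start of support, because Study Procedures places cord clamping at 30 or 60 s. The argument does not depend on it.

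**3. Effect of adjusting for a mediator (illustration).** Assumptions that are not in the documents: treatment shifts one mediator M by d SD, a share s of the effect runs through M, mediation is one-way, and each infant contributes one summary value. With A = 1 for the FiO2 1.0 arm:

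- M = d × A + noise with SD 1
- Y = 150 + (1 − s) × 60 × A + b × M + error, with b = s × 60 / d and a within-arm SD of Y of 70

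The total effect is (1 − s) × 60 + b × d = 60. Once M is in the model, the coefficient of A is (1 − s) × 60:

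- s = 25%: 0.75 × 60 = 45
- s = 50%: 0.50 × 60 = 30
- s = 75%: 0.25 × 60 = 15
- s = 100%: 0

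Simulation with 22 per arm, d = 1 and 4,000 runs per setting gave 44.4, 30.1, 14.9 and −0.2 mL/kg/min when M was always adjusted for. When M was adjusted for only if its own between-arm test was significant, the means were 45, 31, 17 and 3. M was significant in about 83%, 90% and over 99% of runs for d = 0.9, 1.0 and 1.5.

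**4. True baseline variables.** Two of the eight listed characteristics are Apgar scores, which leaves six. If these are independent and each is tested at 5%, the chance of at least one significant difference is 1 − 0.95⁶ = 0.265, about 26%. Leaving out gestational age, which is a stratification factor, gives 1 − 0.95⁵ = 0.226, about 23%. Birth weight tracks gestational age, so independence is only approximate.

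**The case against.** The strongest reply is that the confirmatory result is untouched. The primary test takes no covariates, and the rule feeds only a mixed model listed under secondary outcomes. This stands, and it is the main limit on the harm. A reader might infer that the rule can erase the primary finding, or that an adjusted result would replace it. The documents do not support this: the mention of the primary outcome in the rule is a criterion for relevance, and no section gives the adjusted model precedence.

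A reader might also turn the illustration into a loss of power for the trial. That is not supported either. The protocol states no power for the mixed model, which uses repeated measurements, and both the SpO2 shift and the mediated share are assumed. Both arms are titrated to the same targets, and the Discussion cites a review, graded as low-level evidence, that found no difference between high and low initial FiO2 in the proportion of infants reaching target. The shift could be smaller than 1 SD.

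Adjustment for SpO2 is also not certain. Clinical relevance is a judgement and no variable is named. The rule allows the adjustment and makes it likely if the hypothesis is right, but it does not require it.

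Nor is shrinkage towards zero assured. The Discussion says that oxygenation under non-invasive support can be influenced only when the infant breathes, so SpO2 is partly a consequence of the outcome. With such feedback, or with shared causes of SpO2 and breathing, the direction of bias is uncertain.

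One might finally read the rule as meant for baseline variables only. The wording does not bear this out. It names other study parameters alongside basic characteristics, Other Outcomes uses study parameters for events after birth such as intubation, and the basic characteristics themselves include "Apgar score 1 and 5 min after birth".

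**Conclusion.** The point holds for the secondary linear mixed model. As written, the rule selects covariates by between-arm significance from a list that includes the hypothesised mediator and a near-component of the outcome. If it is followed and such a variable enters, the group effect on minute volume and the other respiratory measures no longer estimates the total effect of initial FiO2.

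Under simple one-way mediation the estimate shrinks in proportion to the mediated share, from 60 to between 45 and 0 mL/kg/min for shares of 25 to 100%. These figures show mechanism and scale under stated assumptions and do not predict this trial's result. For the six true baseline items, the chance of a data-driven adjustment trigger is about 26% under independence, before the relevance judgement is applied.

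This should be fixed, but it does not put the primary analysis at risk.

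**What to change.** Delete the significance-triggered rule. In its place:

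- Name the mixed-model covariates before outcome data are examined, and limit them to variables known before FiO2 starts. The minimum is the gestational-age stratum already used under Randomization.
- State that SpO2, heart rate, mask-ventilation time, share of breaths above 4 mL/kg, Apgar scores and any other measurement after allocation are not covariates in any model that estimates the treatment effect.
- Label any analysis of SpO2 as a mediator exploratory, and report it separately from the group effect.

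Adding centre as a covariate and presenting baseline characteristics without p-values are optional. The change is to analysis wording only and needs no further data or infants.

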### Ethical Considerations

The study will be conducted according to the principles of the Declaration of Helsinki and in accordance with the Medical Research Involving Human Subjects Act (WMO). The study protocol is approved by the ethical committee of the LUMC and AUMC.

### Dissemination of Results

Results of the study will contribute to a manuscript, which will be submitted for publication to a peer-reviewed international medical journal, and will be presented at national and international conferences.

## Discussion

Most preterm infants need additional oxygen during stabilization at birth to achieve appropriate SpO_2_ target ranges (34). Results of a recent meta-analysis demonstrated that persisting hypoxia at 5 min after birth is associated with a higher risk of mortality and the development of an intraventricular hemorrhage, which we should try to avoid (14). Although a recent systematic review showed no differences in percentage of infants achieving SpO_2_ target ranges between infants initiating stabilization with high or low FiO_2_, the level of evidence of these results is low (35). It is therefore still unclear whether the initial FiO_2_ level influences breathing effort, thereby influencing the capacity of preterm infants to reach the target range. However, it has recently became clear that oxygenation can only be influenced in infants supported by non-invasive ventilation in case of presence of spontaneous breathing, as then the larynx opens and an open airway is achieved (9). Before focusing on achievement of SpO_2_ target ranges, we should look at the effect of initiation stabilization with a high FiO_2_ on breathing effort.

The current SpO_2_ target ranges used during stabilization at birth are based on the reference values described by Dawson et al. (27). While these target ranges have been based on data from healthy term and preterm infants, those values might not apply to infants requiring more respiratory assistance at birth. In the current resuscitation guidelines, oxygen titration is recommended if infants fail to achieve the 25th centile of the SpO_2_ reference ranges and are thus hypoxemic in the first minutes after birth (14, 36). Because hypoxia is known to provide inhibitory input into the respiratory center, this effect on respiratory effort has been overlooked with regard to the importance of oxygen titration. It is possible that the compromised preterm infant requiring respiratory support during transition would benefit by higher SpO_2_ reference ranges during stabilization at birth. By initiating stabilization at birth with a FiO_2_ of 1.0, we hypothesize that infants will achieve higher SpO_2_ values in the first minutes after birth, leading to an increase in respiratory effort at birth.

A FiO_2_ of 1.0 should be administered with caution to avoid the detrimental effects of hyperoxia (21, 23, 24). However, in this study the amount of time that infants receive pure oxygen is very limited since FiO_2_ will be titrated according to SpO_2_ values. To evaluate pure oxygen exposure, both the amount of time that infants spent above SpO_2_ target range and the level of 8-iso-prostaglandin F2α indicating oxidative stress will be measured.

While low SpO_2_ values reflect a low oxygenation level in arterial blood, known as hypoxaemia, this does not necessarily represent low oxygen uptake and usage by tissues, particularly cerebral tissues. While pO_2_ gradients drive oxygen diffusion into tissues and pO_2_ levels in blood are related to blood SpO_2_ levels, there are any factors that determine oxygen uptake and usage by tissues. For instance, organs can increase blood flow to maintain oxygen delivery and/or increase oxygen extraction when blood oxygen content decreases. As such, SpO_2_ alone provides limited information on oxygen consumption by tissues at high or low blood oxygen levels. In addition, individual patients might differ from one another in their ability to cope with free radicals released in response to inflammation, hyperoxia, and hypoxia before or after birth (21). Although the study is not powered to detect a difference in oxidative stress, we decided to objectively measure this using 8-iso-prostaglandin F2α as marker of oxidative stress, which indicates the true amount of oxygen exposure.

The reported trials comparing high vs. low levels of oxygen did not report on how oxygenation levels influence respiratory effort. Although the level of respiratory support during stabilization at birth was reported in most trials and shown to be not significantly different, the effectiveness of spontaneous breathing in both infants receiving higher or lower FiO_2_ was not evaluated (18, 37–40). Gaining an adequate level of spontaneous breathing during stabilization at birth to improve the success of non-invasive respiratory support could potentially lead to a lower incidence of intubation and mechanical ventilation in the delivery room, contributing to a lower risk of lung injury in high-risk preterm infants.

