### Sample Size Calculation

There is no data available on measurements of respiratory effort in the first 5 min after birth during stabilization with a FiO_2_ of 1.0 compared to 0.3. In a recent study, the average minute volume of preterm infants over the first 100 breaths was 150 ± 70 mL/kg/min (30). In a retrospective observational study, we observed an 80% relative increase in respiratory drive when FiO_2_ was switched from 0.21 to 1.0, in the first minute after FiO_2_ was increased (from 134 to 240 mL/kg/min). Other parameters of respiratory effort increased as well: average expired tidal volumes (Vt_e_) increased by 37% (from 4.9 to 6.7 mL/kg), and rate of rise to maximum tidal volumes increased by 32% (13.8 to 18.2 mL/kg/s) (15).

However, since we investigate a FiO_2_ of 0.3 instead of 0.21 in the lower oxygen arm, we expect half of the effect (40% relative increase) in respiratory drive than demonstrated in the study of Van Vonderen et al. (15). Therefore, to detect an increase in average minute volume in the first 5 min after birth from 150 to 210 mL/kg/min, using a standard deviation of 70 mL/kg/min, with a power of 80% and an α error of 5% (two tailed test), 22 infants are required for each arm. Given the fact that parents may withdraw their consent or decline deferred consent after the infant is included in the study, or that the recording of physiological measurements fails in 10% of all infants, a total of 50 infants will be recruited (25 in each arm).

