### Study Procedures

Infants will be randomized to start stabilization after birth with an initial FiO_2_ of either 1.0 or 0.3, after which FiO_2_ will be titrated following target SpO_2_ recommended in our local guidelines on stabilization after birth, which are based on the target ranges described by Dawson et al. (27). In both groups, all other procedures in the delivery room and NICU will be performed according to the local and international guidelines, only the initial FiO_2_ setting will be different. Cord clamping will be performed after 30 s in case of an apneic infant, and after 60 s if the infant is breathing at birth.

After the initial FiO_2_ setting, titration will be performed according to the local protocol:

-When SpO_2_ is below target ranges defined by Dawson et al. FiO_2_ will be titrated up to 0.5 and subsequently to 1.0, when the initial FiO_2_ setting was 0.3. In case of an initial FiO_2_ setting of 1.0, FiO_2_ will be maintained at 1.0.-When SpO_2_ is above target ranges, FiO_2_ will be titrated down to 0.5 and subsequently to 0.3 and 0.21. If SpO_2_ is above target ranges when stabilization is initiated with FiO_2_ 0.3, FiO_2_ will be titrated down to 0.21 directly.

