#### Statistical Analysis of Primary Outcome

Differences in average respiratory minute volume in the first 5 min after birth between the study groups will be tested with a Student's *t*-test if the data are found to be parametric, or with Mann-Whitney u-test when the data are non-parametric.

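### The primary comparison is unadjusted although randomisation is stratified by gestational age, and the only covariate rule is driven by significance tests and stays in the mixed model

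*Protocol article*

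**What the plan says.** Four parts of the protocol article bear on this.

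- **Randomization.** Allocation is stratified by gestational age in two bands, 24+0 to 26+6 and 27+0 to 29+6 weeks.
- **Statistical Analysis of Primary Outcome.** "Differences in average respiratory minute volume in the first 5 min after birth between the study groups will be tested". The methods named are the t-test and, for non-normal data, the Mann-Whitney test. Neither uses the stratum or any other covariate.
- **Statistical Analysis of Other Outcomes.** Other parameters and basic characteristics are tested for differences between arms. Those that are significant and clinically relevant to the primary outcome go into the linear mixed model. That model is listed under the secondary outcomes.
- **Sample Size Calculation.** The planned rise is 60 mL/kg/min (150 to 210) and the assumed SD is 70. The stated result reads "with a power of 80% and an α error of 5% (two tailed test), 22 infants are required for each arm".

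Three further places concern breathing state at birth.

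- The Discussion states that "oxygenation can only be influenced in infants supported by non-invasive ventilation in case of presence of spontaneous breathing".
- Study Procedures times cord clamping "after 30 s in case of an apneic infant, and after 60 s if the infant is breathing at birth", so staff must judge the state.
- Other Outcomes says "we will collect basic characteristics such as gestational age, birth weight, mode of delivery" and more, including Apgar scores at 1 and 5 min. Breathing state is not named, but the list is open-ended.

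**The concern.** Stratifying by gestational age implies that the investigators expect it to be prognostic. Stratification balances the arms on it. An analysis that ignores the stratum leaves the between-stratum spread in the error term, so the standard error is larger than it need be.

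The covariate rule does not repair this. A variable earns its place by how strongly it predicts the outcome. A p-value for imbalance between arms does not measure that, and with about 44 evaluable infants such tests detect little. Even a large, significant imbalance would alter only the mixed model and leave the primary result as it was. The rule also covers other study parameters, which include saturation, heart rate and time on facemask ventilation. These are measured after treatment starts, so the model could end up adjusting for part of the effect.

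In a trial of 50 infants with a single physiological primary outcome, this is avoidable loss of precision and avoidable data-dependence.

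**Working it through.** **1. The plan's own figure.** Inputs from Sample Size Calculation: difference 210 − 150 = 60, SD 70, two-sided 5%, power 80%.

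- n per arm = 2 × (1.960 + 0.842)² × 70² / 60² = 21.4, rounded up to 22. This reproduces the stated number. The exact t-test solution is 22.4, which rounds to 23; the gap is trivial.
- 22 / 0.90 = 24.4, rounded up to 25 per arm, 50 in total. This also reproduces.
- Power at 22 per arm: SE = 70 × √(2/22) = 21.1; 60 / 21.1 = 2.84; Φ(2.84 − 1.96) = 81.1%. By the t distribution it is 79.3%.

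The sample size contains no arithmetic error, and the unadjusted test delivers its stated power if the average effect is 60.

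**2. What a pre-specified prognostic covariate would add.** The share of variance explained, R², is not in the documents and is assumed. Residual SD = 70 × √(1 − R²); the effect is held at 60 and n at 22 per arm. The last column shows the mean gap between two strata that each R² implies, assuming strata of equal size: gap = 70 × 2 × √R².

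| R² (assumed) | Residual SD | Power (normal) | Power (t) | n per arm for 80% | Implied gap, mL/kg/min |
|---|---|---|---|---|---|
| 0 | 70.0 | 81.1% | 79.3% | 22 | 0 |
| 0.05 | 68.2 | 83.1% | 81.3% | 21 | 31 |
| 0.10 | 66.4 | 85.0% | 83.3% | 20 | 44 |
| 0.20 | 62.6 | 88.8% | 87.4% | 18 | 63 |
| 0.30 | 58.6 | 92.5% | 91.3% | 15 | 77 |

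The gain runs from about 2 to 11 points. The upper rows need a gap between strata as large as the planned treatment effect or larger, so for gestational age alone the lower rows are the safer expectation.

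**3. Breathing state as a covariate.** The apneic share f and the deficit G in minute volume are not in the documents. Assumed: f = 20% to 40%, G = 35 to 70 mL/kg/min, total SD kept at 70. Then R² = f(1 − f)G² / 70², which is 0.04 to 0.06 at G = 35 and 0.16 to 0.24 at G = 70. Simulation (6,000 trials per setting, 22 per arm, effect 60 in every infant) gives:

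| f | G | Unadjusted | Adjusted |
|---|---|---|---|
| 20% | 35 | 78.9% | 79.8% |
| 30% | 35 | 79.0% | 79.9% |
| 40% | 35 | 79.9% | 80.9% |
| 20% | 70 | 79.8% | 85.8% |
| 30% | 70 | 80.2% | 87.2% |
| 40% | 70 | 79.4% | 87.9% |

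The gain is about 1 point at G = 35 and 6 to 9 points at G = 70, which is a full SD.

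**4. Could effects by breathing state be separated?** Assume an effect of 60 in breathing infants and 0 in apneic infants. The SE of the interaction is SD × √(2/(22f) + 2/(22(1 − f))).

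| f | SE (SD 70) | Power | Power with R² = 0.3 (SD 58.6) |
|---|---|---|---|
| 0.1 | 70.4 | 13% | 17% |
| 0.2 | 52.8 | 21% | 27% |
| 0.3 | 46.1 | 26% | 34% |
| 0.5 | 42.2 | 30% | 40% |

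Even with the state recorded, an interaction of this size would usually be missed.

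**The case against.** The strongest reply is that nothing here is an error. An unadjusted comparison of randomised arms is a valid test of the average effect of the starting FiO2, and the stated sample size gives the stated power for it. Power is lost only relative to a better analysis, by an amount that rests on assumptions. That stands, and it limits the point to precision and pre-specification. It does not rescue the covariate rule, which the article states outright and which is poor on its own terms.

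A reader might infer something stronger: that breathing state is a pre-exposure marker which has to be in the primary model, and that its absence is why a diluted effect could not be told from no effect. The article does not support this, for four reasons.

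- **Timing and blinding.** Study Procedures does not say that the judgement is recorded, or when the allocated gas starts relative to it. It comes within the first minute after birth, inside the 5-minute outcome window. The clinician in charge of the procedure also randomises, so it may be made knowing the arm.
- **Mechanism.** The Discussion sentence concerns oxygenation. It does not say that an infant apneic at the start stays unresponsive for 5 min. Setting the effect to zero in such infants over the whole average is an extreme case; at assumed apneic shares of 10% to 30% it would cut unadjusted power to about 73% to 51% (normal approximation).
- **Size.** The article says only that most preterm infants breathe at birth. It gives no apneic share and no deficit.
- **Cause.** The interaction is underpowered with or without the covariate. The limit is the number of infants. The planned analyses of minute volume and diaphragm activity over time already give some information on breathing, though after exposure.

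**Conclusion.** The point holds as a weakness in precision and pre-specification. The primary test ignores the stratification factor, and the only route for covariates depends on a significance test for imbalance and ends in a secondary model. The primary comparison is not biased by this, and the sample size stands.

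The size of the loss cannot be derived from the documents. It is about 2 points of power at an assumed R² of 0.05 and about 11 points at 0.30. For breathing state, under assumed apneic shares of 20% to 40% and deficits of 35 to 70 mL/kg/min, adjustment would move power from about 79% to 80–88% if the effect is the same in all infants.

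That possible gain does not justify putting a post-randomisation, possibly unblinded judgement into the primary model. It does justify recording the state and using it in a sensitivity analysis.

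**What to change.** - **Primary analysis.** Replace the unadjusted test by a pre-specified linear model of the 5-min average minute volume/kg on arm and gestational-age stratum. Use it whether or not the arms differ, and report the adjusted difference with its 95% CI.
- **Covariate rule.** Delete the rule that selects covariates by significance. Any covariate in the mixed model should be named in advance and measured before treatment.
- **Breathing state.** Record the apneic or breathing judgement already made for cord clamping, with its time and the time the allocated gas starts. Add it as a covariate in a sensitivity analysis only. Report treatment effects by breathing state with 95% CIs, labelled exploratory.

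The cost is a few lines of analysis wording and a small addition to the case report form. The stratum is already known from randomisation. Sample size and care are unchanged.
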